### Trial design

In order to study the efficacy of the group reminiscence intervention, a between-subjects design will be used, with two experimental conditions and repeated measures across baseline, post-intervention, and three months post-intervention. Specifically, we will compare the following conditions. Experimental group: individuals will participate in group reminiscence meetings dealing with specific phases of their lives; they will share their memories and listen to the ones related by the other participants. Control group: individuals will participate in group conversations about current events.

Informed consent will be obtained from each participant. Psychometric outcomes will serve as quantitative dependent variables.

### Randomization

The present study is a randomized controlled trial. Participants will be randomly assigned to one of the two groups of the trial, balanced on gender and pre-test scores.

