**CONSORT flow diagram.**

### Sample size calculation

The number of participants was calculated in order to have a sufficient size to prove the effect of training, reducing type two (false negative) statistical errors. The limit of 0.05 will be used for type one errors (false positive).

Sample size calculation used an assumption that participants in the experimental group would report improvements, based on outcome over time, and that these effects would differ from those achieved in the control group. As noted in the introductory section, previous evaluations of this kind of reminiscence intervention have produced moderate effect sizes [20, 21]. Accordingly, we estimated a sample size for a moderate treatment effect over time. We calculated sample size by using a repeated-measures analysis of variance across time (pre-post) with an α level set at 0.05 (two-tailed), statistical power level (1-β) of 0.80, and an estimate of correlation among repeated measures of 0.5. The calculation, based on GPower 3 (Heinrich-Heine-Universität, Düsseldorf, Germany) [22], led us to estimate minimum sample size of 40 participants (or 20 per group).

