### Trial analysis

Data analyses will use IBM SPSS Statistics software (IBM, Armonk, USA). Descriptive methods will be used to demonstrate the consistency of the two groups, to describe participants’ characteristics, and to report levels of participation and dropout. Analysis of variance will compare baseline characteristics of the two groups involved in the study, and determine overall significance of improvement across the outcome measures.

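### Allocation is balanced on gender and pre-test scores, but the stated ANOVA uses the pre-test score only through change, does not mention gender, and adds uninformative baseline tests

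*Protocol article*

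**What the plan says.** On allocation, the protocol article (Randomization) states: "Participants will be randomly assigned to one of the two groups of the trial, balanced on gender and pre-test scores". It does not say which pre-test score is meant, or by what mechanism the balance is achieved.

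On analysis, the Trial analysis section states: "Analysis of variance will compare baseline characteristics of the two groups involved in the study, and determine overall significance of improvement across the outcome measures". The Trial design section describes a between-subjects design "with two experimental conditions and repeated measures across baseline, post-intervention, and three months post-intervention", so baseline is one level of the repeated measure. The Sample size calculation section uses the same model with two time points (pre and post), a two-sided alpha of 0.05, power of 0.80 and a correlation of 0.5 between repeated measures, and arrives at 40 participants, 20 per group.

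No section names a covariate, and gender does not appear in any described outcome analysis. Descriptive methods are planned for participants' characteristics, and the ANOVA of baseline characteristics comes on top of them.

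**The concern.** There are two problems, and they should be kept apart.

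- **Efficiency.** Subtracting the pre-test score is only one way of using it, and at moderate correlation it is a poor one. Change scores force a slope of 1 on the pre-test, whereas ANCOVA estimates the slope. With 20 per arm the difference is noticeable.
- **Mismatch between allocation and analysis.** When allocation makes the arms alike on a prognostic score, the difference between arms varies less from trial to trial. A test that leaves that score out of the model does not see this, so its standard error is too large and its real error rate falls below the nominal one.

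The baseline tests add nothing. In a properly randomized trial any baseline difference is due to chance, and on variables that allocation was meant to equalise the test has even less to say.

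**Working it through.** **Inputs.** N = 40 (20 per arm), two-sided alpha 0.05, power 0.80 and correlation ρ = 0.5, all from Sample size calculation. Outcome SD is set to 1 at both times. The effect size is given only as moderate, so a range is shown.

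**The plan's own figure.** For the pre-post group-by-time test, noncentrality is f² × N × 2/(1 − ρ) with 1 and N − 2 df. With f = 0.25 (assumed), 34 participants suffice (power 0.807) and 40 give 0.869. With f = 0.23 the answer is 40 (power 0.809); f = 0.20 gives 52 and f = 0.30 gives 24. As no f is stated, 40 is neither confirmed nor shown wrong. In this setup f = 0.25 equals a 1.0 SD difference in change: 0.0625 × 40 × 2/0.5 = 10, and 1.0² × 40/4 = 10.

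**Residual variance per participant**
- Post score only: 1.00
- Change score (identical to the pre-post group-by-time test): 2(1 − ρ) = 2 × 0.5 = 1.00
- ANCOVA on the pre-test score: 1 − ρ² = 1 − 0.25 = 0.75

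The ratio of ANCOVA to change is (1 + ρ)/2, so the saving is 35% at ρ = 0.3, 25% at 0.5, 15% at 0.7 and 10% at 0.8.

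**Scenario A: simple randomization.** The standard error of the arm difference is √(1.00 × 2/20) = 0.316 for change and √(0.75 × 2/20) = 0.274 for ANCOVA. By the noncentral t distribution, the difference detectable with 80% power is 0.91 SD (38 df) and 0.79 SD (37 df). Power at N = 40:

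| True difference | Change score | ANCOVA |
|---|---|---|
| 0.5 SD | 0.34 | 0.43 |
| 0.57 SD | 0.42 | 0.53 |
| 1.0 SD | 0.87 | 0.945 |

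**Scenario B: allocation balanced on that outcome's pre-test score.** If the arms have nearly equal pre-test means, the difference in change is nearly the difference in post scores with the pre-test part removed. Its true variance is then about 0.75 × 2/20 = 0.075, as for ANCOVA. The unadjusted test still uses 1.00 × 2/20 = 0.100. Its critical value of 2.02 therefore acts like 2.02/√0.75 = 2.34, which a null trial exceeds about 2.5% of the time.

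Simulation (N = 40, ρ = 0.5, no effect) agrees:

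| Allocation | Real type I error, change score |
|---|---|
| Simple | about 5% |
| Pairs matched on another score (assumed correlation 0.5 with this one) | about 4.3% |
| Stratified by median split of this score | 3.2–3.7% |
| Pairs matched closely on this score | 2.4–2.6% |

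ANCOVA stays at 5% under simple allocation and under close pairing. The simulated variance of the change-score estimate is 0.100 under simple allocation (ANCOVA 0.077) and 0.076 under close pairing (ANCOVA 0.075).

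Simulated power at 0.5 SD, change score to ANCOVA: 0.34 to 0.42 (simple), 0.33 to 0.43 (median split), 0.31 to 0.43 (close pairing). At 1.0 SD, where little room is left, it goes from 0.87 to 0.94 (simple) and from 0.90 to 0.94 (close pairing).

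**Gender.** The article gives no association between gender and any outcome, so no gain can be computed.

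**The case against.** The article's analysis section is three sentences long, and a full plan may name covariates. That stands: the silence does not prove that none will be used. What remains is what the text does commit to, namely a repeated-measures ANOVA on which the sample size also rests and a significance test of baseline characteristics.

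A reader might infer three stronger things, and the documents support none of them.

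- *That the pre-test score is ignored.* It is not. Baseline is a level of the repeated measure and enters every outcome comparison through change. The weakness is inefficient use.
- *That baseline testing takes the place of the outcome analysis.* The same sentence goes on to "determine overall significance of improvement across the outcome measures", so the baseline test is an addition.
- *That the trial loses 25% in variance and also runs at about 2.5% type I error.* The former belongs to simple randomization and the latter to close pairing on the outcome's own score. They cannot both hold. The article states no mechanism, and close balance on four outcome scales plus gender among 40 people who are still being recruited is hard to achieve, so the real error rate may lie nearer 5%.

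It is also fair to say that 0.5 is a planning value and that the variance saving shrinks to 10–15% at correlations of 0.7 to 0.8. The saving remains positive at any correlation below 1.

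**Conclusion.** The point holds as one of efficiency and of matching analysis to allocation, not of validity. The planned test is unbiased and does not inflate false positives. At ρ = 0.5 it extracts no more from the pre-test score than a comparison that leaves it out and, to the extent that allocation is balanced on that score, it is conservative.

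With 40 participants, adjustment adds about 8 to 12 points of power at 0.5 SD whichever allocation is assumed, and about 5 to 7 points at 1.0 SD. It does not rescue an underpowered comparison: at 0.57 SD, the pooled effect on depressive symptoms cited in the Background and used here as a difference in change, power reaches only 0.53. The figures rest on equal SDs at both times, normal outcomes, no dropout, and the plan's correlation of 0.5. The contribution of gender is unknown and may be small.

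**What to change.** For each outcome, prespecify the between-arm difference at post-intervention and at three months, estimated by ANCOVA or the equivalent mixed model, with that outcome's pre-test score and gender as covariates. State which pre-test scores the allocation balances on and how, so that the model can be seen to match it. Drop "Analysis of variance will compare baseline characteristics of the two groups involved in the study" as a significance test and report baseline characteristics descriptively by arm.

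The cost is a change of wording and one or two error degrees of freedom out of 38. No further participants, visits or measurements are needed, since both covariates are already collected for allocation.

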### Protocol

The intervention will last six weeks. Each week participants in both the experimental group and the control group will attend a group setting; in the experimental condition, participants will share their memories with peers, and in the control condition, participants will talk about current news.

### Setting

The guidelines reported in group reminiscence literature [28] will be followed to structure our reminiscence intervention. Each meeting will include six participants and last 60 minutes. Two clinical psychologists will lead the sessions. The physical setting will be in the nursing home; a comfortable room will be provided, accessible to wheel-chairs, and participants will sit in a circle. The facilitating psychologists will encourage involvement of each participant, in order to stimulate the discussion or debate in a positive atmosphere. Personal criticism, moral judgments, and political statements will be averted. The detailed protocol is described below, for both the experimental and the control group.

#### Experimental group

Participants will be assured that all the memories shared during the sessions will be confidential and will not be disclosed outside of the group. Every session will incorporate a theme, recalling specific autobiographic experiences in a chronological order. From the first to the sixth meeting, the topics will be best memory, childhood, school years, war, job, and holiday. Participants will be encouraged to bring photos or objects related to past themes. At the end of each meeting, the theme of the following session will be disclosed. The researchers can also bring materials as cues for reminiscence.

#### Control group

Every meeting will offer topics for discussion taken from newspaper and newscasts. Personal opinions will be promoted, and links with the daily life of participants will be welcome (everyday activities and personal preferences). A group discussion about these various themes will take place in every meeting from the first to the sixth. The main goal is to stimulate social interaction and communication, without discussing either personal events from the past or private memories. Final individual meetings will be scheduled for participants in both groups in order to administer the questionnaire and collect feedback from the users.

### Trial analysis

Data analyses will use IBM SPSS Statistics software (IBM, Armonk, USA). Descriptive methods will be used to demonstrate the consistency of the two groups, to describe participants’ characteristics, and to report levels of participation and dropout. Analysis of variance will compare baseline characteristics of the two groups involved in the study, and determine overall significance of improvement across the outcome measures.

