## Methods/Design

### Aim of the study

Based on the need for further randomized controlled trials in this area, the present study aims at assessing the effects of group reminiscence on psychosocial wellbeing in institutionalized, non-demented elderly individuals. First, we will examine the specific effects of simple reminiscence as compared to a placebo intervention in which participants are engaged in everyday conversations (discussion of current events). The findings of previous meta-analyses are inconclusive on this issue. The review carried out by Bohlmeijer *et al*. [9] found no significant differences between studies that used an active placebo and those that used a wait-list condition. In contrast, the Pinquart and Forstmeier meta-analysis [6] observed larger improvements in positive wellbeing if the control condition received no intervention as compared to standard conversation, indicating that socialization activities can also bring about positive emotional states.

Second, we intend to assess the impact of reminiscence on a broad range of psychosocial outcome indicators, including depression symptoms, positive wellbeing (self-esteem, life satisfaction), and quality of life. Since we aim to evaluate the specific effectiveness of simple reminiscence by comparing it to conversation on current events, clinically depressed residents will not be included in the trial. More specifically, we will examine four hypothesis. Hypothesis one is that we expect an improvement of self-esteem, evaluated through the Rosenberg Self-Esteem Scale [15], in the experimental group by the end of the protocol when compared to the control group. Hypothesis two is that we expect an increase of life satisfaction, evaluated through the Life Satisfaction Index [16], in the experimental group by the end of the protocol when compared to the control group. Hypothesis three is that we expect an increase of the perceived quality of life, evaluated through the WHOQOL-Old Scale [17], in the experimental group by the end of the protocol when compared to the control group. Finally, hypothesis four is that we expect a decrease of depressive symptoms, measured through the Geriatric Depression Scale (GDS) [18], in the experimental group by the end of the protocol when compared to the control group. Further, we will assess whether these expected improvements in mental health and psychological well-being are maintained during a three-month follow-up period.

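### The stated efficacy analysis, an ANOVA for overall improvement, names no between-arm comparison at the end of the intervention, although every hypothesis is one

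*Protocol article*

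**What the plan says.** Four parts of the protocol article bear on which test decides efficacy.

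- **Aim of the study.** Each of the four hypotheses (self-esteem, life satisfaction, quality of life, depressive symptoms) expects a change "in the experimental group by the end of the protocol when compared to the control group". Persistence is a further question: "we will assess whether these expected improvements in mental health and psychological well-being are maintained during a three-month follow-up period".
- **Sample size calculation.** The trial is sized on a pre-post repeated-measures ANOVA, assuming that the experimental group improves and that "these effects would differ from those achieved in the control group".
- **Trial design.** The design is between-subjects, "with two experimental conditions and repeated measures across baseline, post-intervention, and three months post-intervention".
- **Trial analysis.** This is the only statement of the analysis. ANOVA has two uses: to compare the baseline characteristics of the two groups, and to "determine overall significance of improvement across the outcome measures". The groups are named for the first use and not for the second.

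The Randomization section adds that allocation is balanced on gender and pre-test scores. Neither appears in the analysis statement.

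**The concern.** The trial exists to separate what reminiscence does from what ordinary group conversation does. The Aim section reports a meta-analytic finding on conversation controls, "indicating that socialization activities can also bring about positive emotional states", so some improvement in the control arm is foreseeable. If both arms improve, a test of improvement can be significant while the specific effect of reminiscence is nil.

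The article does state a criterion for efficacy. As worded, that criterion does not carry through the comparison that the hypotheses state, and a reader cannot tell which F-test decides success. At stake is a claim for reminiscence that the control arm would have earned equally. A lesser cost is the precision lost by leaving out the pre-test score and gender on which the allocation is balanced.

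**Working it through.** **Inputs.** From Sample size calculation: 40 participants (20 per arm), two-tailed alpha 0.05, power 0.80, correlation ρ = 0.5. Assumed here: SD 1 at every visit and equal correlation between visits. The article calls the effect moderate and gives no number, so a range is used.

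**1. The plan's own figure.** For the pre-post arm-by-time test, λ = f²·N·m/(1−ρ) with m = 2 and 1 and N−2 df.

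- With the conventional moderate f = 0.25, λ = 0.0625 × 40 × 2/0.5 = 10 and power at N = 40 is 0.869. The smallest N reaching 0.80 is 34.
- N = 40 gives exactly 0.80 at f = 0.227.
- In this 2×2 layout the between-arm difference in change is d = 4f, so f = 0.25 is 1.0 SD and f = 0.227 is 0.91 SD.

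The 0.91 SD is therefore solved back from N = 40 and is not stated in the article. That 40 does not follow from f = 0.25 is a separate matter and does not show 40 to be wrong.

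**2. Both arms improve equally, no arm difference.** For the time effect, λ = N·Σ(μₜ − μ̄)²/(1−ρ). Over three visits the gain is taken as held at follow-up. With a gain of 0.5 SD:

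- Pre-post: Σ = 0.25² + 0.25² = 0.125; λ = 40 × 0.125/0.5 = 10; F(1, 38) critical value 4.10; probability of significance 0.87.
- Three visits: Σ = 0.5² × 2/3 = 0.167; λ = 40 × 0.167/0.5 = 13.3; F(2, 76) critical value 3.12; probability 0.90.

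The 0.5 SD is an assumption. The same formulas give:

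| Gain in both arms | Time test, pre-post | Time test, three visits | Between-arm contrast |
|---|---|---|---|
| 0.2 SD | 0.23 | 0.23 | 0.05 |
| 0.3 SD | 0.46 | 0.47 | 0.05 |
| 0.4 SD | 0.69 | 0.73 | 0.05 |
| 0.5 SD | 0.87 | 0.90 | 0.05 |

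**3. What baseline adjustment is worth.** A change score has SD √(2(1−ρ)) = 1. A baseline-adjusted post score has SD √(1−ρ²) = √0.75 = 0.866. The standardized difference therefore rises from d to d/0.866 (for example 0.91/0.866 = 1.05). Two-sided noncentral t, 20 per arm, 38 df for change and 36 after two covariates, with gender taken as unrelated to outcome:

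| True arm difference | Change contrast | Adjusted contrast |
|---|---|---|
| 0.5 SD | 0.34 | 0.43 |
| 0.91 SD | 0.80 | 0.90 |
| 1.0 SD | 0.87 | 0.94 |

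**4. Conditional check on missing visits.** Suppose a classical three-visit repeated-measures ANOVA on complete rows were used, and some residents missed only the three-month visit. At an assumed 10, 20 or 30% loss, equal in both arms, 36, 32 or 28 of 40 stay in the analysis. The pre-post contrast at 1.0 SD then has power 0.83, 0.78 or 0.72. It would be 0.87 if all 40 post-intervention scores were used.

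**The case against.** The strongest reply is that the between-arm intent is plain elsewhere. Each hypothesis is stated against the control group, the sizing assumes that change differs between arms, and the design is called between-subjects. The only ANOVA described in any detail is pre-post, and in that 2×2 model the arm-by-time interaction is exactly the between-arm difference in change at the end of the intervention. An analyst who followed the sizing section would run the right test. This stands, and it limits the point: no sentence names a pooled time effect as the test of efficacy, so 0.87 to 0.90 is the error rate of one literal reading and not of the plan as a whole. It does not remove the point, because the one sentence that fixes the analysis omits the comparison.

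Three stronger readings are tempting and are not supported.

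- **That the plan prescribes an omnibus test over three visits.** In the Trial analysis sentence, overall refers to the outcome measures. The three visits come from Trial design.
- **That such a test would generally cost power.** At 0.91 SD the two-df interaction has power 0.71 if half the effect remains at three months, but 0.84 if it is fully kept or fully lost, against 0.80 for the pre-post contrast. The direction depends on the pattern.
- **That anyone who misses a visit is dropped.** The article states no such rule. It says only that dropout will be reported, and a condensed article may leave missing-data handling to the full protocol or analysis plan. Step 4 is a conditional risk only.

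**Conclusion.** The point holds as a fault in how the efficacy criterion is fixed. The analysis sentence tests improvement without an arm term or a time point, while the hypotheses and the sizing call for a between-arm comparison at the end of the intervention. Taken literally, it would be met in 87 to 90% of trials in which both arms gained 0.5 SD and reminiscence added nothing, and in about 23% if both gained 0.2 SD. The between-arm contrast stays at 5% throughout. These figures rest on the article's 20 per arm and correlation of 0.5, on equal correlation across visits, and on an assumed common gain.

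Leaving out the pre-test score and gender is a smaller, second cost. At the article's correlation, adjustment is worth 7 to 10 percentage points of power over the range 0.5 to 1.0 SD.

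A reader should not infer that the trial will claim success without a specific effect, or that its analysis will be confined to completers. The document shows neither.

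**What to change.** Replace the efficacy clause in Trial analysis with the following content.

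1. For each of the four hypotheses, the test is the experimental-minus-control difference at post-intervention, adjusted for pre-test score and gender, with everyone analysed in the arm to which they were randomized.
2. The three-month arm difference is reported with its 95% CI as a separate maintenance contrast.
3. Time effects and within-arm changes are descriptive and are not evidence of efficacy.

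A linear mixed model in SPSS delivers both contrasts: arm, visit, arm-by-visit, pre-test score and gender as fixed effects, fitted to all available post-intervention and three-month scores. It also avoids the conditional risk, since a resident without a three-month score still contributes at post-intervention. If ANOVA is kept, an analysis of covariance at post-intervention with the same two covariates is enough for the first item.

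The cost is a few lines of wording, in the software already named, with no new data and no change to visits or sample size. The change should be made before outcomes are analysed by arm.
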